#### Intention-To-Treat Analyses

Intention-to-treat analyses [81,82] will be conducted to understand the extent to which participants who satisfy the inclusion criteria for enrollment and are therefore randomized to one of the two conditions (intention-to-treat population) are similar to participants who provided complete data across the measurement rounds (actually treated sample). The purpose of intention-to-treat analyses is to scrutinize whether the conclusions drawn from the RCT remain robust even after considering participant attrition across time [81]. We will adhere to the recommended guidelines for performing multiple imputation on clinical research data [83].

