### Statistical Analysis

#### Power

Power analyses were performed using *P*<.05 (2-tailed) at .80 power, based on recommended guidelines [78-80]. The power analyses were conducted for each statistical technique to be pursued in aims 1 to 3: mixed (between-subjects and within-subjects) multivariate analysis of variance (MANOVA), mixed (between-subjects and within-subjects) analysis of variance, independent 2-sided *t* test, dependent 2-sided *t* test, correlation, and the mediational models involving structural equation modeling (based on the β coefficient). The pilot study collected similar measures from pregnant/postpartum women with a history of major depressive disorder who used SB or HALO TB. Hence, the power analyses were based on pilot sleep and mood data. Calculations revealed an average effect size across all postpartum timepoints (T1 to T6) between the treatment and control groups on the following measures: infant sleep (*d*=0.39), postpartum sleep quality (*d*=0.27), and postpartum depression (*d*=0.33). Based on these effect sizes, a sample size of 208 participants is needed for infant sleep, 434 participants for postpartum sleep quality, and 286 participants for postpartum depression to attain statistical significance. Thus, a final sample size of 393 participants will be targeted (allowing for an attrition rate of 15%).

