#### Mean Differences

Initial analyses will be performed to verify that the random assignment procedure successfully equalized participants between the treatment and control groups on the preintervention variables. Thus, MANOVA will compare these 2 groups on the entire set of preintervention baseline measures. A chi-square test will verify that both groups have the same distribution of infant boys and girls. As participants will be randomized to groups using a random number generator, baseline equivalency of the 2 groups is anticipated.

Six separate mixed 2 (treatment vs control) × 6 (assessment period) MANOVA models will be conducted. Specifically, to assess hypothesis 1a (aim 1), the model (model 1) will be applied to the infant sleep quality outcome measures. To address hypothesis 1b (aim 1), the analysis (model 2) will be applied to maternal postpartum sleep quality outcome measures. To evaluate hypothesis 2a (aim 2), the model (model 3) will be applied to the maternal postpartum depression outcomes. To examine hypothesis 3a (aim 3), the model (model 4) will be estimated on the measures involving peripheral cytokines, immune cells, and stimulated cytokine profiles. To examine hypothesis 3b (aim 3), the model (model 5) will be undertaken on the measures of T-cell dysfunction. Furthermore, to examine the exploratory aim, the model (model 6) will be estimated on the epigenetic biomarkers.

In each of the mixed MANOVA models, several follow-up analyses will be conducted to examine the results. First, a mixed (between-subjects and within-subjects) analysis of variance will be applied on each specific outcome. Second, independent 2-sided *t* tests will assess mean differences between the treatment and control group (at each timepoint) on each outcome. Third, dependent 2-sided *t* tests will permit scrutiny of the temporal change in mean scores between every 2 timepoints on every outcome. Fourth, the longitudinal trajectories across the entire 6-month period for both the treatment and control groups will be graphed using 95% CIs to provide a visual tool to offer insights to understand the effectiveness of the RCT.

Prior to conducting analyses, the normal distribution of all the measures will be inspected. If a variable is evidenced to be nonnormally distributed, then the bootstrapping variant of these statistical techniques instead will be performed to obtain corrected *P* values [84].

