### Missing Data

Attrition in our prior studies has been approximately 15%, and we have accounted for that in our planned sample size. In addition, in our prior studies, we have missing biological data (due to incomplete blood draws) in about 7% of the visits; we anticipate similar rates in this study, which will use the same approach. Given the prospective nature of our study, we will carefully evaluate missingness. If identified, we will employ one of the two strategies to handle missing data. The first approach relies on a technical assumption of missing at random and involves inclusion of covariates related to missingness in all analyses. Full information maximum likelihood performs well under ignorable missing data conditions such as missing at random. A second strategy we will use is multiple imputation. Although this has the potential to yield biased estimates dependent on the nature of missingness [97], we will employ this approach to implement sensitivity analysis under plausible assumption of missing not at random to examine the robustness of our inference [98].

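### Intention-to-treat is cast as a secondary check against completers, and no missing-data method is tied to the main mixed MANOVA

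*Protocol article*

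**What the plan says.** All references are to the protocol article.

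- **Intention-To-Treat Analyses.** These analyses are to show how far the randomized population and completers agree: randomized women "are similar to participants who provided complete data across the measurement rounds (actually treated sample". The section adds: "The purpose of intention-to-treat analyses is to scrutinize whether the conclusions drawn from the RCT remain robust even after considering participant attrition across time". It closes by committing to published guidance on multiple imputation.
- **Mean Differences.** "Six separate mixed 2 (treatment vs control) × 6 (assessment period) MANOVA models will be conducted". These models carry the hypotheses on infant sleep, maternal sleep and maternal depression. No analysis set is named.
- **Missing Data.** After missingness has been evaluated: "If identified, we will employ one of the two strategies to handle missing data". The first strategy assumes data missing at random, adds covariates related to missingness, and refers to full information maximum likelihood. The second is multiple imputation, which is then given the job of a missing-not-at-random sensitivity analysis. Expected attrition is about 15%, and about 7% of visits are expected to lack blood data.
- **Patient Adherence.** Bassinet use is measured separately, by self-report, photographs and comments.

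**The concern.** Intention-to-treat should fix whom the primary analysis includes and in which arm they are counted: all randomized women, as assigned. Here it is a test of whether conclusions hold up after attrition. Those conclusions must then come from some other analysis, and the only other sample that the section names is women with complete data.

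The label given to that sample is also wrong. Complete data and treatment received are different things. Under the label, a mother who stops using the bassinet but returns every questionnaire counts as treated, and one who uses it for six months but misses one round does not. The article itself expects bassinet use to vary while data collection continues to month 6 (Telephone Interview and Screening).

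The choice of main model makes this matter. Each month asks for questionnaires, a week of diaries, and actigraphy on mother and infant. A conventional mixed MANOVA needs every round and every outcome in the set. The trial is unblinded, so staying in it may depend on symptoms and on the arm. The headline could then describe compliant completers and not the randomized comparison.

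**Working it through.** **1. Do the stated methods reach the main model?**

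| Method | Where it is named | Role given | Tied to the MANOVA? |
|---|---|---|---|
| Multiple imputation | Intention-To-Treat Analyses | Part of the robustness check | No |
| Full information maximum likelihood | Missing Data | Missing-at-random strategy | No; it suits the structural equation models but is not how a conventional mixed MANOVA is fitted |
| Multiple imputation | Missing Data | Missing-not-at-random sensitivity analysis | No |
| Generalized estimating equations | Statistical Analyses for Immune Measurements | Longitudinal immune models | No |

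The two strategies under Missing Data are offered as alternatives, yet they do different jobs: one is a main-analysis method and the other a sensitivity analysis.

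**2. Reproducing the plan's sizing.** Inputs, all from Power: "Power analyses were performed using *P*<.05 (2-tailed) at .80 power"; effects "infant sleep (*d*=0.39), postpartum sleep quality (*d*=0.27), and postpartum depression (*d*=0.33"; result "a sample size of 208 participants is needed for infant sleep, 434 participants for postpartum sleep quality, and 286 participants for postpartum depression".

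n per arm = 2(1.960 + 0.842)²/d², rounded up, then doubled:

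- d = 0.39: 104 per arm, 208 in total (stated 208)
- d = 0.27: 216 per arm, 432 in total (stated 434)
- d = 0.33: 145 per arm, 290 in total (stated 286)

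All are within 3%, so the plan sized a single two-group comparison. The same formula is used for power below.

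**3. Power if only completers are analysed.** Power = Φ(d·√(N/4) − 1.960). The article gives both 342 and 393 as the sample size, so both are shown.

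- 0.85 × 342 = 291. Depression: 0.33 × √72.75 − 1.960 = 0.855, power 0.80 (0.86 with all 342).
- 0.85 × 393 = 334. Depression: 0.33 × √83.5 − 1.960 = 1.056, power 0.85 (0.905 with all 393).

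**4. Adding missed single rounds (assumption).** Completers = N × 0.85 × (1 − m)⁶, with misses independent across six rounds. The article gives no rate for missed questionnaires. The upper value, 7%, borrows its blood-draw rate; the lower value, 2%, is purely assumed.

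| m per round | Completers of 342 | Depression power | Completers of 393 | Depression power |
|---|---|---|---|---|
| 0% | 291 | 0.80 | 334 | 0.85 |
| 2% | 258 | 0.75 | 296 | 0.81 |
| 5% | 214 | 0.67 | 246 | 0.73 |
| 7% | 188 | 0.62 | 216 | 0.68 |

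**5. Bias (illustrative simulation).** Assumptions: true d = 0.33 in every month, within-woman correlation 0.5, and 15% dropout overall. Where dropout is symptom-related, its log-odds rise by 1 per SD of the previous month's score. The completer estimate of the six-month mean difference is:

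- dropout unrelated to symptoms: 0.33
- related equally in both arms: 0.31
- related in the control arm only: 0.23
- related in the smart-bassinet arm only: 0.43

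**The case against.** The strongest reply is that nothing in the article says the MANOVA runs on complete cases. The intention-to-treat section itself names multiple imputation, and a MANOVA on imputed data keeps every randomized woman. Missing Data plans a missing-at-random approach for all analyses and already includes missing-not-at-random imputation. It can be read as a primary method plus a sensitivity analysis, not as a choice made after the data are seen. Adherence is measured separately, and women who develop a mood or anxiety disorder stay in the study. The article is condensed, and the exact analysis set is often left to a SAP.

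Much of this stands. A reader might infer that a complete-case primary analysis is prescribed; the text does not support that. It supports only that the text permits one and points towards it. What does not fall to this reply is the definition of intention-to-treat, which is written down and wrong. Nor does the reply supply a sentence linking any missing-data method to the MANOVA.

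A reader might also take 0.62 as the expected power. It is one end of an assumed range. It uses the smaller sample size, applies a blood-draw rate to a web questionnaire that blocks skipped items (though not missed months), and assumes independent misses; clustered misses would lose fewer women. It also follows the single-comparison sizing. If d = 0.33 holds in each month and the within-woman correlation is 0.6, the six-month mean has variance (1 + 5 × 0.6)/6 = 0.667. The arm main effect then has power of about 0.79 at 188 women and 0.93 at 291.

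Finally, a reader might infer that completer analysis must weaken the treatment effect. Loss of power is certain under such an analysis. The estimate, however, can shrink or grow depending on which arm loses its more symptomatic women.

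**Conclusion.** The point holds in this form: intention-to-treat is misdefined as a secondary check, completers are mislabelled as the treated sample, and the missing-data methods are not attached to the main model. Following the text can therefore produce a completer-based headline result.

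If it does, the stated 15% attrition alone leaves depression power at about 0.80 (291 of 342) or 0.85 (334 of 393), so attrition by itself does not take depression below the design level. Missed single rounds could lower it to 0.75-0.62 or 0.81-0.68, given the assumed 2% to 7% per round, independence, and the plan's single-comparison formula. Bias has no assured direction: 0.23 to 0.43 for a true 0.33 under assumed dropout mechanisms. These figures show what is exposed; they are not forecasts. The definition bears on the primary sleep and mood outcomes and should be settled before outcome data are examined.

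**What to change.** 1. Define the primary analysis as all randomized women in their assigned arm, whatever their bassinet use.
2. Fit a likelihood-based linear mixed model for repeated measures (arm, month, arm × month) to every available month. Alternatively, keep the planned MANOVA and run it on multiply imputed data. Either meets the concern; name one in advance.
3. Keep the missing-not-at-random imputation already planned, as the prespecified sensitivity analysis and not as an alternative to the primary method.
4. Drop the treated label for women with complete data. Report completers, and separately bassinet adherers as measured under Patient Adherence, as supportive only.

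The cost is a change of wording in the protocol and SAP and, for the mixed model, a different procedure in standard software. No extra data or participants are needed.

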#### Mean Differences

Initial analyses will be performed to verify that the random assignment procedure successfully equalized participants between the treatment and control groups on the preintervention variables. Thus, MANOVA will compare these 2 groups on the entire set of preintervention baseline measures. A chi-square test will verify that both groups have the same distribution of infant boys and girls. As participants will be randomized to groups using a random number generator, baseline equivalency of the 2 groups is anticipated.

Six separate mixed 2 (treatment vs control) × 6 (assessment period) MANOVA models will be conducted. Specifically, to assess hypothesis 1a (aim 1), the model (model 1) will be applied to the infant sleep quality outcome measures. To address hypothesis 1b (aim 1), the analysis (model 2) will be applied to maternal postpartum sleep quality outcome measures. To evaluate hypothesis 2a (aim 2), the model (model 3) will be applied to the maternal postpartum depression outcomes. To examine hypothesis 3a (aim 3), the model (model 4) will be estimated on the measures involving peripheral cytokines, immune cells, and stimulated cytokine profiles. To examine hypothesis 3b (aim 3), the model (model 5) will be undertaken on the measures of T-cell dysfunction. Furthermore, to examine the exploratory aim, the model (model 6) will be estimated on the epigenetic biomarkers.

In each of the mixed MANOVA models, several follow-up analyses will be conducted to examine the results. First, a mixed (between-subjects and within-subjects) analysis of variance will be applied on each specific outcome. Second, independent 2-sided *t* tests will assess mean differences between the treatment and control group (at each timepoint) on each outcome. Third, dependent 2-sided *t* tests will permit scrutiny of the temporal change in mean scores between every 2 timepoints on every outcome. Fourth, the longitudinal trajectories across the entire 6-month period for both the treatment and control groups will be graphed using 95% CIs to provide a visual tool to offer insights to understand the effectiveness of the RCT.

Prior to conducting analyses, the normal distribution of all the measures will be inspected. If a variable is evidenced to be nonnormally distributed, then the bootstrapping variant of these statistical techniques instead will be performed to obtain corrected *P* values [84].

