## Methods

### Study Design

This study is a 2-arm, parallel-group RCT. Participants will be randomized at 1:1 ratio to either SB group or TB group. Outcomes are assessed at 7 timepoints (Figure 1): late pregnancy (P3) and in postpartum months 1-6 (M1-M6).

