**Maternal assessments (primary)**														
	Sleep diary			✓		✓		✓		✓		✓		✓
	Actigraphy			✓		✓		✓		✓		✓		✓
	Pittsburgh Sleep Quality Index	✓		✓		✓		✓		✓		✓		✓
	Edinburgh Postnatal Depression Scale	✓		✓		✓		✓		✓		✓		✓
	Generalized Anxiety Scale	✓		✓		✓		✓		✓		✓		✓
	Tasso blood collection kit (Epigenetics)	✓												
	Blood samples (inflammation)	✓						✓						✓

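### The 2 × 6 models for maternal EPDS and PSQI state no adjustment for the late-pregnancy score that the trial collects, which gives up precision

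*Protocol article*

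**What the plan says.** All references are to the protocol article.

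- **Study Design:** "Outcomes are assessed at 7 timepoints (Figure 1): late pregnancy (P3) and in postpartum months 1-6 (M1-M6").
- **Table 1, primary maternal assessments:** the rows for PSQI, the "Edinburgh Postnatal Depression Scale" and the Generalized Anxiety Scale are ticked at baseline and at every postpartum month. The maternal sleep diary and maternal actigraphy are ticked at months 1 to 6 only. So are the infant measures.
- **Mean Differences, main models:** "Six separate mixed 2 (treatment vs control) × 6 (assessment period) MANOVA models will be conducted". Model 2 covers maternal sleep quality and model 3 maternal depression. The follow-up mixed ANOVAs and the t tests at each timepoint are described without covariates.
- **Mean Differences, use of baseline:** "Thus, MANOVA will compare these 2 groups on the entire set of preintervention baseline measures". The stated purpose is to verify that randomisation equalised the arms, and no action is tied to the result.
- **Additional Factors to Consider and Use as Covariates:** household, feeding, infant, bedtime-routine, childhood-trauma and delivery factors. No baseline score of an outcome scale appears.
- **Statistical Analyses for Immune Measurements:** these models adjust for baseline severity of depressive symptoms.

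**The concern.** A pre-randomisation measurement of the same scale is the natural covariate for a randomised comparison of that scale. According to the Telephone Interview and Screening section, participants complete the baseline questionnaires before they are assigned. The late-pregnancy score is therefore a legitimate covariate and should be nearly complete.

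The 2 × 6 layout has no place for it. Late pregnancy is not a level of the time factor and is not named as a covariate. The balance test does not replace adjustment. It does not alter the treatment estimate, and it leaves any chance imbalance in the comparison.

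What is at stake is the width of the confidence intervals and the power for two main maternal scales. It matters most for maternal sleep quality, where the article's own requirement of 434 participants exceeds both sample sizes it gives (342 and 393).

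**Working it through.** **Inputs from the article**

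- Error rates (Power): "Power analyses were performed using *P*<.05 (2-tailed) at .80 power".
- Effect sizes (Power): "infant sleep (*d*=0.39), postpartum sleep quality (*d*=0.27), and postpartum depression (*d*=0.33").
- Their basis (Power): "Calculations revealed an average effect size across all postpartum timepoints (T1 to T6) between the treatment and control groups". No baseline adjustment is mentioned.
- Stated requirement (Power): "a sample size of 208 participants is needed for infant sleep, 434 participants for postpartum sleep quality, and 286 participants for postpartum depression".
- Allocation 1:1 and attrition 15%. The article gives two sample sizes: 342 (Abstract, Participants) and 393 (Power). Completers are 342 × 0.85 = 290.7, about 291, or 393 × 0.85 = 334.05, about 334.

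**Input assumed**

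- Correlation r between the late-pregnancy score and the postpartum quantity being compared. The article does not give it. The range used is 0.3 to 0.6.

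**Step 1: reproduce the plan's own figures**

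Total N = 2 × ceiling[2 × (1.960 + 0.842)² / d²] for an unadjusted two-group comparison.

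| Outcome | d | Normal formula | t-based | Stated |
|---|---|---|---|---|
| Infant sleep | 0.39 | 208 | 210 | 208 |
| Maternal sleep quality | 0.27 | 432 | 434 | 434 |
| Depression | 0.33 | 290 | 292 | 286 |

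All are within about 3% of the stated figures. The sample size therefore takes no credit for a baseline covariate.

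**Step 2: effect of adjustment on variance**

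Residual variance is multiplied by 1 − r². For r = 0.3 / 0.4 / 0.5 / 0.6 this gives 0.91 / 0.84 / 0.75 / 0.64, a reduction of 9 / 16 / 25 / 36%. The standardised effect becomes d / √(1 − r²). At r = 0.6 and d = 0.27 it is 0.27 / 0.8 = 0.3375.

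**Step 3: power, two-sample t test, two-sided 0.05**

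| Scale, completers | No adjustment | r=0.3 | r=0.4 | r=0.5 | r=0.6 |
|---|---|---|---|---|---|
| PSQI, d=0.27, 291 | 63% | 67% | 71% | 75.5% | 82% |
| PSQI, d=0.27, 334 | 69% | 73% | 77% | 81% | 87% |
| EPDS, d=0.33, 291 | 80% | 84% | 86.5% | 90% | 94% |

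**Step 4: total N for 80% power (normal formula)**

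- PSQI: 432 unadjusted, then 392 / 362 / 324 / 276 for r = 0.3 / 0.4 / 0.5 / 0.6.
- EPDS: 290 unadjusted, then 264 / 244 / 218 / 186.

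At r = 0.5 the PSQI requirement (324) falls below 334 completers but stays above 291.

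**Step 5: which outcomes can gain**

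Table 1 gives a late-pregnancy value for PSQI, EPDS and the Generalized Anxiety Scale. In model 2 only PSQI can be adjusted for its own baseline. The figure d=0.27 is given for postpartum sleep quality, and applying it to PSQI is an assumption.

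**The case against.** **This is efficiency, not error.** The unadjusted comparison is unbiased and agrees with the unadjusted sample-size calculation. That stands, and it limits the weight of the point.

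**Covariates may be left to an analysis plan.** The covariate list is introduced as inclusive, so absence from it proves little by itself. The Missing Data section also allows covariates related to missingness, which might bring baseline scores in. But the article does fix the factorial form, the number of periods, the use of baseline and the follow-up tests. A later plan that followed this text would carry the unadjusted models forward.

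**The gain rests on an assumed r.** This stands. Current depressive or anxiety disorder is an exclusion, and the Limitations section itself worries about a narrow range of mood symptoms. Both could lower r for EPDS. At r = 0.2, power for PSQI with 291 completers rises only from 63% to 65%, and for EPDS from 80% to 82%.

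**The balance test is not worthless.** In an unblinded trial with assignment by a coordinator, a gross imbalance could point to a failure of allocation. That is a reason to look at baseline, and a descriptive table allows it.

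**Stronger readings that the article does not support**

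- *Baseline is used nowhere except the balance test.* The immune models adjust for baseline depressive severity. The Figure 2 caption labels month 3 as T4, so the cross-lagged model appears to start in late pregnancy. The statement holds for the mean-difference plan only.
- *All maternal sleep outcomes gain.* Diary and actigraphy have no late-pregnancy value.
- *Anxiety is affected in the same way.* GAD-7 is collected at baseline, but none of the six models clearly analyses it.
- *The immune model 5 has the same defect.* Blood is drawn at baseline, month 3 and month 6, and aim 3 concerns the trajectory from late pregnancy. Baseline may already be a time level there.

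**Conclusion.** The point holds for EPDS and PSQI in the 2 × 6 mean-difference models. Both scales are measured before randomisation, and the models neither include that measurement nor state an adjustment for it. A reader might infer a biased treatment effect, but randomisation protects the unadjusted comparison.

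The size depends on r, which is assumed. For r between 0.3 and 0.6, the gain for PSQI is about 4 to 19 percentage points of power with 291 completers and 4 to 18 with 334. For EPDS with 291 completers it is about 4 to 14 points, and possibly less if the exclusion criteria narrow the baseline range. These are two-sample approximations using the article's averaged effect sizes, not a simulation of the full mixed model. The change should be made because it costs almost nothing and helps most where the trial is weakest.

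**What to change.** 1. In model 2, add the late-pregnancy PSQI as a covariate in the PSQI analysis, including its follow-up ANOVA.
2. In model 3 and its follow-up ANOVA, add the late-pregnancy EPDS as a covariate.
3. If GAD-7 is analysed in a comparable model, adjust it for its late-pregnancy value in the same way.
4. Replace the baseline MANOVA and the chi-square test of infant sex by a descriptive table by arm.
5. Leave the models for infant outcomes, maternal diary and maternal actigraphy as they are on this point, and leave model 5 unchanged.

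The cost is a change of wording, best made before any outcome data are compared by arm. No new visit, measurement or participant is needed. Each covariate uses about one degree of freedom, so little is lost if r turns out to be low.
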